### Background measures

Each participant will be asked to complete questionnaires including background information on demographics and employment history.

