### Outcome measures

#### Primary outcome: competitive employment

The primary outcome of the SEED-trial is *competitive employment at any time during the 12 months after enrollment in the study*. Competitive employment is here defined as working in a job on the competitive labor market, at usual wages, with regular supervision.

Additionally, success in employment will be defined using a range of standardized indicators of employment outcomes used in IPS studies [40], including rate of job acquisition, amount and duration of work, total wages, and number of days from enrollment in the study to employment. Information about receipt of social security benefits (sickness and disability benefits, unemployment, work assessment allowance), income, financial assistance, and educational activity (started or completed education), will also be collected.

We will use three sources of information for competitive employment: Survey data for hours worked and success in employment; register data from the NAV for receipt of social security benefits and income; and register data from Statistics Norway (SSB) for financial assistance and educational activity.

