### Data collection and data management

Survey data will be collected at baseline, 6 and 12 months. Baseline questionnaires will be administered at the information meetings, and participants complete their information electronically on iPads with secure software (Qualtrics®), or in paper format if preferred. Follow-up questionnaires will be administered electronically to participants providing their e-mail address at baseline, or in paper format via regular mail.

Data collected using iPads will automatically be electronically transferred to and stored in a secure online database. Data collected in paper form will be entered manually by the data manager at Uni Research Health and sent to the same database, after which the original questionnaires will be stored in a locked filing cabinet.

Register data will be collected retrospectively for 3 years before baseline, and for a 5-year period after enrollment date. The information will be de-identified and merged with survey data, while the identifier is secured in a locked and fireproof safe.

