#### Statistical analyses

Assessment of treatment effects will be analyzed using standard statistical methods, including t-tests for continuous data and chi-square tests for categorical data. Logistic regression will be performed to study potential moderators of treatment effects. For repeated measures over time (e.g. for sick leave), the statistical analyses may be extended to generalized estimation equations (GEE), to account for correlated data. All analyses will follow the intention to treat principle.

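### The only test named for the binary primary outcome is an unadjusted chi-square; prognostic baseline data are collected but not used to sharpen the treatment estimate

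*Protocol article*

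**What the plan says.** The primary outcome is "competitive employment at any time during the 12 months after enrollment in the study", a yes/no variable for each participant. For treatment effects, the Statistical analyses section names "standard statistical methods, including t-tests for continuous data and chi-square tests for categorical data". The text then moves straight on to regression, which has a separate purpose: "chi-square tests for categorical data. Logistic regression will be performed to study potential moderators of treatment effects". GEE is mentioned as a possible extension for repeated measures. No covariate-adjusted estimate of the main effect is named.

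The article also describes data that could serve as covariates:

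- Background measures: participants are asked to fill in "questionnaires including background information on demographics and employment history".
- Data collection and data management: "Baseline questionnaires will be administered at the information meetings". Under Recruitment and randomization, ID numbers are randomised after those meetings, so these answers precede allocation.
- Data collection and data management: "Register data will be collected retrospectively for 3 years before baseline, and for a 5-year period after enrollment date". The Primary outcome section describes the NAV register data as covering social security benefits and income.

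Recruitment and randomization describes computer-generated 1:1 lists and nine NAV offices, and mentions no stratification factor.

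**The concern.** Eligibility is broad: unemployed people under 30 on temporary benefits for a range of social or health reasons. Earlier attachment to work probably varies among them and probably predicts finding a job. If the main effect is estimated without that information, two things follow. The interval is wider than the collected data allow, and any chance difference between arms in prior employment stays in the point estimate. That estimate is used again, because the Cost-benefit analysis section multiplies the treatment effect by productivity gains.

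**Working it through.** **Inputs.** From Sample size calculation: 61% and 23% employed, 5% significance, 90% power, 31 per group needed, 124 planned (62 per arm at 1:1). Sidedness is not stated; two-sided is assumed. The article gives no prognostic strength for any covariate and no smaller effect, so the values used for these below are assumptions.

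**1. The plan's own figure.** Unpooled two-proportion formula:

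n = (1.960 + 1.282)² × (0.61×0.39 + 0.23×0.77) / 0.38² = 30.2, rounded up to 31.

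The stated 31 per group is reproduced. (The pooled-variance version gives 34.)

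**2. Unadjusted power at 62 per arm, control rate 23% (pooled-variance formula).**

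| True difference | Power |
|---|---|
| 38 points (61% vs 23%, planned) | 99.4% |
| 30 points (assumed) | 94% |
| 25 points (assumed) | 84% |
| 20 points (assumed) | 66% |
| 15 points (assumed) | 44% |

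**3. Chance imbalance.** For a baseline factor with 50% prevalence (assumed), the between-arm difference has SD = √(2 × 0.25 / 62) = 0.090, or 9 points. A gap beyond about 1.96 × 9 ≈ 18 points occurs in about 1 trial in 20. If people with the factor find work 25 points more often (assumed), an 18-point gap moves the unadjusted risk difference by 0.18 × 25 = 4.5 points, and a gap of one SD by about 2.3 points.

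**4. Precision at the planned rates.** SE = √((0.61×0.39 + 0.23×0.77)/62) = 0.0818, so the 95% interval is ±16.0 points. If covariates explain a share R² of outcome variance, SE is multiplied by √(1 − R²):

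- R² = 0.10 (assumed): ±15.2 points, 5% narrower.
- R² = 0.20 (assumed): ±14.3 points, 11% narrower.

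**5. Power by the same approximation at 43% vs 23% (assumed).** SE = √((0.43×0.57 + 0.23×0.77)/62) = 0.0825 and power is 67.9% (unpooled). It becomes 72.4% with R² = 0.10 and 77.3% with R² = 0.20.

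**6. Simulation.** 62 per arm, 2,000 runs per scenario, one standard-normal covariate. The Pearson chi-square is compared with a likelihood-ratio test of arm in the adjusted logistic model. Simulation error is about 1 point.

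| Rates | Log-odds per SD (assumed) | Chi-square | Adjusted |
|---|---|---|---|
| 61% vs 23% | 0 to 1.5 | 99–100% | 99–100% |
| 48% vs 23% | 0 | 83.8% | 83.6% |
| | 0.5 | 84.3% | 86.5% |
| | 1.0 | 84.5% | 90.0% |
| | 1.5 | 84.0% | 94.0% |
| 43% vs 23% | 0 | 67.3% | 67.6% |
| | 0.5 | 64.9% | 67.4% |
| | 1.0 | 66.4% | 74.4% |
| | 1.5 | 66.8% | 79.6% |
| 23% vs 23% (no effect) | 0 to 1.5 | 3.8–4.7% | 4.5–5.8% |

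For a prognostic covariate the gains run from 2.3 points (86.5 − 84.3, before rounding) to 12.8 points (79.6 − 66.8). Under no effect the adjusted test rejected about 1 point more often, so a small part of the smaller gains may reflect calibration rather than information. The simulation tests the arm coefficient; it does not evaluate a standardised risk difference, for which steps 4 and 5 are the guide.

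**The case against.** Four counter-arguments deserve weight.

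*The list is open.* The methods are introduced with a word that makes them examples, and no primary test is named as such. A reader might infer that the protocol fixes an unadjusted chi-square as the sole primary analysis. The text does not go that far: the link is made through outcome type, and a fuller plan may say more. What remains is that the section pairs regression with moderators and the main effect with simple tests, and in that allocation adjustment of the main effect has no place. The absence of a stated stratification factor is silence in a condensed article and cannot be counted as a flaw.

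*The method is sound.* A reader might infer bias or an invalid test. Neither is supported: under 1:1 randomisation the chi-square holds its level (3.8–4.7% in the simulation), and its p-value already allows for chance imbalance. This objection stands in full.

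*The trial is not underpowered on its own figures.* Also correct. Power is about 99% at 61% versus 23%, and adjustment adds almost nothing there. The 124 was chosen to allow subgroup analyses. The smaller effects used above are not in the document. They are plausible only because the rates come from earlier IPS studies, while the article says this population has not been studied.

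*The covariates may be weak or incomplete.* For a single 50%-prevalent binary factor at 43% versus 23%, average within-arm variance is (0.2451 + 0.1771)/2 = 0.211. R² = 0.10 then needs a gap of √(0.0211/0.25) = 29 points in employment between those with and without it, and R² = 0.20 needs √(0.0422/0.25) = 41 points. Those are strong predictors, and many participants are too young for a long work record. A reader might also assume that the register gives paid work directly; the article lists benefits and income, so prior work would have to be derived from income. Nor does asking participants for employment history guarantee an answer from all of them.

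**Conclusion.** The point holds as an efficiency matter. The article names only an unadjusted test suited to its binary primary outcome and reserves regression for moderators, while baseline data that are likely prognostic are collected before allocation or, for the register, describe a period that allocation cannot affect. The cost of leaving this as it stands is an interval perhaps 5–11% wider than necessary (if R² is 0.10–0.20) and an estimate exposed to a chance imbalance with an SD of about 9 points for a 50%-prevalent factor. Power suffers only if the true difference is well below 38 points: roughly 2 to 13 points of power at differences of 20–25 points, for assumed covariate log-odds of 0.5–1.5 per SD, and nothing if the covariate is not prognostic. Naming the covariates in advance also removes the option of choosing them after results are known.

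**What to change.** In Statistical analyses, state that the primary analysis is a logistic regression of 12-month competitive employment on arm plus a short, named set of baseline covariates: prior employment from the baseline questionnaire or prior income from the NAV register (with the definition given), gender and age. Report the result as a standardised risk difference with 95% CI. Keep the chi-square test as the supporting unadjusted analysis, and leave the moderator regressions as a separate exercise.

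The set should stay small. At 43% versus 23% about 0.43×62 + 0.23×62 ≈ 41 participants would have the outcome, or about 10 for each of four coefficients (arm and three covariates).

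The cost is a wording change, slightly more analysis work and a rule for missing baseline questionnaire items. No new data collection and no extra participants are needed.

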#### Cost-benefit analysis

Economic returns will be calculated based on treatment effects obtained from the statistical analyses, and will be evaluated using a standard cost benefit formula [56–58], as used by Hagen et al. [59].

Benefit will be measured in terms of increases in the net present value of production, as indicated by an increase in labor market participation. This is calculated as the product of the treatment effect, i.e. the increase in labor market participation and the productivity gains for the society when a person is employed as opposed to receiving social security benefits. Cost of the intervention is measured by treatment cost and costs related to follow-up outside the intervention in the different treatment groups. Health care utilization will be measured using survey data from the participants providing information about health and use of health services.

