#### Interventions

Both interventions in this trial are offered by VR organizations overseen by the NAV, and are part of the various employment schemes offered to people on temporary benefits in Norway. Participants continue to receive temporary benefits while attending the services, which are normally offered for up to two or three years, depending on the specific intervention and individual needs.

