##### Traditional Vocational Rehabilitation (TVR)

The first group will be referred to a TVR organization, where they will receive a traineeship in a sheltered business with follow-up from trained advisors and department supervisors.

This intervention is *service as usual* for the study participants, and is currently offered to clients who are considered by their caseworker to have need for special assistance to obtain work. The specific approach falls within the *train-then-place principle*, and participants receive preparatory work training in a sheltered environment before pursuing employment. The goal of the intervention is to improve the participant’s work skills and opportunities for entering the labor market, and includes follow-up geared towards finding a job. The traineeships are offered by various sheltered businesses in the area with a range of departments including canteens and catering, car repair, day-care services, upholstery and interior decoration, transport, laundry services, welding, and warehouse handling. The distribution of participants to the various departments will follow usual practice, and is conducted at NAV based on the individual caseworker’s description of the client’s interests and goals, as well as availability and waiting-lists.

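### The cost-benefit formula has no term for what trainees produce in sheltered businesses, an output that only the TVR arm has, and does not say whether TVR cost is net of it

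*Protocol article*

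**What the plan says.** All references are to the protocol article.

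- **What is valued** (Cost-benefit analysis): "Benefit will be measured in terms of increases in the net present value of production, as indicated by an increase in labor market participation".
- **How it is computed** (same section): the treatment effect, meaning the rise in participation, multiplied by the "productivity gains for the society when a person is employed as opposed to receiving social security benefits". The section says that returns "will be evaluated using a standard cost benefit formula", citing sources but not printing the formula.
- **Cost side** (same section): "Cost of the intervention is measured by treatment cost and costs related to follow-up outside the intervention in the different treatment groups".
- **What counts as employment** (Primary outcome: competitive employment): "working in a job on the competitive labor market, at usual wages, with regular supervision".
- **Income status during the services** (Interventions): "Participants continue to receive temporary benefits while attending the services". This applies to both arms.
- **What TVR participants do** (Traditional Vocational Rehabilitation): "they will receive a traineeship in a sheltered business with follow-up from trained advisors and department supervisors". The businesses have "a range of departments including canteens and catering, car repair, day-care services, upholstery and interior decoration, transport, laundry services, welding, and warehouse handling".
- **What SE participants do** (Supported Employment): the section rules out sheltered and preparatory work and aims directly at ordinary jobs.

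**The concern.** The economic endpoint is production, but the formula recognises only two states: employed, or on benefits. A TVR trainee in a laundry or a car-repair department is on benefits, and so falls in the same state as an SE participant who is still looking for a job. The first is placed in a working business and the second is not. For this comparator, a contrast of employment with benefits therefore does not measure the difference in production between the arms.

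The cost side may add to the imbalance. TVR cost plausibly includes the supervision and running of the sheltered departments. If that cost is entered gross, TVR is charged for the departments and gets no credit for what they produce. At stake is the economic comparison of the new service with service as usual, which the abstract announces as part of the trial.

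**Working it through.** **1. The plan's own figures.** The Cost-benefit analysis section gives no number to reproduce. The only rates available are those in Sample size calculation, 61% for IPS and 23% for controls, and they are used here for illustration only.

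**2. Where each participant falls in the formula.**

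| Participant | Competitive job? | On benefits? | Work in a sheltered business? | State in the formula |
|---|---|---|---|---|
| SE, employed | yes | – | no | employed |
| SE, not employed | no | yes | no | on benefits |
| TVR, employed | yes | – | – | employed |
| TVR, in traineeship | no | yes | **yes** | on benefits |

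The second and fourth rows share a state, although only the fourth has sheltered output.

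**3. Formulas.** Let G be the productivity gain from a competitive job. Let s be the value of sheltered output as a share of G, over and above what a non-employed SE participant produces. Let f be the fraction of non-employed TVR time spent in traineeships. The article gives none of G, s or f; s and f are assumed.

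- Benefit per person as written: (0.61 − 0.23) × G = 0.380 G.
- Benefit with sheltered output credited: [0.38 − (1 − 0.23) × f × s] × G = (0.38 − 0.77 f s) × G.

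**4. Results.**

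| s | f | 0.77 f s | Corrected benefit | As-written figure too high by |
|---|---|---|---|---|
| 0 | any | 0 | 0.380 G | 0% |
| 0.10 | 0.5 | 0.0385 | 0.342 G | 0.380/0.3415 − 1 = 11% |
| 0.10 | 1 | 0.077 | 0.303 G | 0.380/0.303 − 1 = 25% |
| 0.25 | 0.5 | 0.096 | 0.284 G | 34% |
| 0.25 | 1 | 0.1925 | 0.188 G | 0.380/0.1875 − 1 = 103% |
| 0.50 | 0.5 | 0.1925 | 0.188 G | 103% |
| 0.50 | 1 | 0.385 | −0.005 G | not defined |

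With f = 1 the gross benefit vanishes at s = 0.38/0.77 = 0.49.

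**5. Output common to both arms is harmless.** If everyone on benefits produced the same share u of an employee's output, the benefit would be 0.38 × (1 − u): 0.342 at u = 0.10 and 0.285 at u = 0.25. That only rescales the unit gain, which a contrast of employment with benefits already allows for. Output found in one arm only does not cancel.

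**6. The cost side can carry the same correction.** Write R = 0.77 f s G for the value of sheltered output.

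- Credited as TVR production: (0.38 G − R) − (C_SE − C_TVR).
- Deducted from TVR cost: 0.38 G − [C_SE − (C_TVR − R)].

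The two are equal. With gross TVR cost and no credit, R drops out and SE's net benefit is too high by R. With both adjustments, R is subtracted twice.

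**7. Limits of the illustration.** The 0.38 is a difference in ever being employed within a year, treated here as full-year output, whereas f is a share of time. The planned analysis uses a present value; services normally run for up to two or three years, and register follow-up lasts five. Over a longer horizon the percentages could differ greatly.

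**The case against.** The strongest reply is that the article states a relative gain and prints no formula. A reader might infer that it assigns zero production to anyone not employed. It does not: it leaves the level of the benefits state open, and that state can include people in traineeships. This stands. The defect is that one state serves both arms, not that a zero is written down.

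A reader might also infer that SE's net benefit is certain to be overstated. That does not follow either. It requires sheltered output of positive value and a TVR treatment cost entered gross of sales. The article gives no output or sales figure and describes the traineeship as preparatory training. If cost is entered net, the output is already counted and a further credit would count it twice. This stands too, so the conclusion is conditional.

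It can further be said that valuation inputs belong in the fuller plan. That is fair for wage rates, discounting and the exact sensitivity range. It does not remove the point, because the article itself fixes the benefit as a specific product, and that product cannot hold output that only the comparator arm has.

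Finally, the percentages rest on unsourced inputs. They do, and they show only that the omission need not be negligible.

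**Conclusion.** The point holds in conditional form. The stated product omits any production specific to the TVR arm, so on the benefit side the error, if there is one, favours SE. It carries through to the net result unless TVR treatment cost is already net of the sheltered businesses' sales, on which the article is silent.

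The size is unknown. The 11% to 103% range for the gross benefit assumes s of 0.10 to 0.25, f of 0.5 to 1, the planning rates, and ever-employment standing in for full-year output. The point is confined to the cost-benefit analysis and leaves the employment comparison and the required number of participants unchanged. It is a cheap improvement worth making before the economic analysis is run.

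**What to change.** Choose one of two routes and state it:

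1. Define benefit as the between-arm difference in total production, including output from sheltered traineeships in the TVR arm, with TVR treatment cost entered gross.
2. Keep the benefit term as it is and enter TVR treatment cost net of the sheltered businesses' sales attributable to participants.

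Say explicitly that the output is counted exactly once. Under either route, report a sensitivity analysis over an assumed productivity per traineeship month, with zero in the range. If cost was always meant to be net, one sentence saying so settles the main analysis.

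The price is one added input (traineeship months, with provider sales or an assumed productivity) and a few lines of text. SE's cost-benefit figure may come out less favourable. Randomization, the questionnaires on health outcomes and the primary analysis need no change.

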## Discussion

The SEED-trial will provide new knowledge about the effect of TVR versus SE in increasing labor market participation among young unemployed with various social- and health related problems. It will be the first RCT to look at SE for this important and vulnerable group at risk of being excluded from the labor market even before they have had the chance to establish themselves on the labor market.

## Abbreviations

APS, traineeship in a sheltered business; IPS, individual placement and support; NAV, Norwegian labor and welfare administration; RCN, Research Council of Norway; RCT, randomized controlled trial; REC, Norwegian Regional Committees for Medical and Health Research Ethics; SE, Supported Employment; SSB, Statistics Norway; TMG, trial management group; TSC, trial steering committee; TVR, Traditional Vocational Rehabilitation
